### Sample collection and classification

2.5

The peripheral blood will be collected in the morning. Blood samples will be taken from the acupuncture and the control groups before and after treatment; then, the participants from both groups will be asked to wait for 30 min after the blood clotted at room temperature; serum will be collected after centrifuging at 3,000 g for 10 min at 4°C and will be stored at −80°C for proteomic analysis and ELISA validation. In total, 10 blood samples will also be taken from 10 gender- and age-matched healthy people for proteomic analysis.

### Interventions

2.6

All groups will receive the basic treatment of ACI according to the Chinese guidelines for the diagnosis and treatment of acute ischemic stroke 2018, including monitoring and controlling for high blood pressure, sugar metabolic disorder, high cholesterol, and risk factors such as diabetes. The acupuncture and sham acupuncture groups will also receive an additional 30 min of acupuncture therapy as bedside treatment by three acupuncturists who had been trained for at least 3 years and have a master’s degree with more than 5 years of clinical experience, 6 days per week for 2 weeks (12 sessions in total).

#### Acupuncture points

2.6.1

ACI belongs to the “apoplexy” category of traditional Chinese medicine. Traditional Chinese medicine theory believes that the brain is the capital of the *gods*, and the imbalance of *yin* and *yang* and the disorder of *qi* and *blood* lead to the occurrence of apoplexy. Therefore, we choose *dumai* as the main meridian for the treatment of apoplexy concerning its pathway and indications. *Renzhong* (DU26), *Baihui* (DU20), and *Fengfu* (DU16) are three acupoints that are located on the *dumai* and used commonly for the treatment of apoplexy. In addition, *Jingbi* (Ex-HN-21) is also chosen for improving the motor function of the trouble side. The position of acupoints is in accordance with the name and location of Acupoints (a standard of The People’s Republic of China, GB/T12346-2006, 2006). Details of selected acupoints are shown in Table 1.

**Table 1 tab1:** Location of the acupoints.

Points	Location
DU16	On the posterior midline, directly below the external occipital protuberance, in the depression between the origins of the trapezius muscle
DU20	At the junction of a line connecting the apices of the ears and the midline, 5 cun (≈100 mm) from the anterior or 7 cun (≈140 mm) from the posterior hairline
DU26	At the junction of the upper 1/3 and middle 1/3 of the philtrum
Ex-HN-21	1 cun (≈20 mm) superior to the junction of the proximal and middle third of the clavicle

#### Manipulations

2.6.2

Participants in the acupuncture group will be asked to adopt a supine position, breathe normally, and relax their whole body for 2 min, and then, the acupuncture needle will be swiftly inserted into DU26 toward the nasal septum at a depth of 0.3–0.5 cun (≈6–10 mm) with bird-pecking needling until the eyes become wet or developed tears. After this, DU20 will be punctured at an approximately 15⁰ angle to a depth of 0.8–1.2 cun (≈16–24 mm), with the needle rotated for at least 200 revolutions per minute for 1 min. For the DU16, needles will be punctured to a depth of 0.8–1.0 cun (≈16–20 mm), with the lifting, thrusting, and twirling manipulation to attain deqi (a sensation of soreness, aching, heaviness, swelling, or numbness) (MacPherson and Asghar, 2006; Zhou et al., 2011). Finally, the acupuncture needle will be vertically inserted into Ex-HN-21 at a depth of 0.3–0.5 cun (≈6–10 mm) with the lifting-manipulation on a small scale and then removed the needle if the sensation obtained (an electric sensation from the arm to the finger). Sterile, single-use filiform needles will be used in the treatment, with a length of 25 to 40 mm and a diameter of 0.25 mm, manufactured by Suzhou Medical Appliance in Jiangsu Province of China.

The number of needles and duration of treatment in the sham acupuncture group will identical in the acupuncture group, except for any manipulations (without retaining the needle to activate the *qi*). The sham DU26 point was 1 cun (≈20 mm) lateral to DU26, the sham DU20 point was 1 cun (≈20 mm) lateral to DU20, the sham DU16 point was 1 cun (≈20 mm) lateral to DU16, and the sham Ex-HN-21 point was 1 cun (≈20 mm) lateral to Ex-HN-21.

Participants in the sham acupuncture group will also probably choose the same acupoints as the acupuncture group, and participants will not be encouraged to use other therapies for management of ACI throughout the trial. Details will be documented if other therapies used.

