### Randomization and blinding

2.3

The eligible participants will be enrolled and divided randomly in the acupuncture group (received acupuncture), the control group (received no acupuncture), or the sham acupuncture group (received sham acupuncture) at a ratio of 1:1:1 (*n* = 132) using a computer-generated randomization method. Random numbers were put into an opaque envelope and sealed, and the corresponding serial numbers were affixed to the surface of the envelope for random grouping and concealing. The envelopes were opened according to the order in which the subjects were enrolled for grouping and treatment. The patients will be informed whether they will receive acupuncture treatment or not.

The participants in the acupuncture group and sham acupuncture group will be blinded, while those in the control group will not be. Due to the particularity of acupuncture treatment, it is impossible to blind the acupuncturists in this study. All study personnel including the outcome assessors and data analysts will be blinded to the treatment allocation.

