#### Primary outcomes

2.7.1

The primary outcome we chose in this study is the NIHSS score that will be measured before and after treatment to evaluate the neurological deficit. There are 15 items in the scale including consciousness, best gaze, motor arm, facia palsy, motor leg, limb ataxia, sensation ability, dysphagia, and neglect. The score of each item scores range from 0 to 4, and the total scores range from 0 to 42. A higher score indicate a more severe neurological deficit.

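### Needling and adverse-event recording, as written, put the stated blinding of participants and assessors at risk for an examiner-scored primary outcome

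*Protocol article*

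**What the plan says.** Section 2.3 (Randomization and blinding) makes two claims. For participants: "The participants in the acupuncture group and sham acupuncture group will be blinded, while those in the control group will not be". For staff: "All study personnel including the outcome assessors and data analysts will be blinded to the treatment allocation". It also says that patients will be told whether or not they are to receive acupuncture.

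Section 2.6.2 (Manipulations) describes delivery. In the real arm, DU26 is needled "with bird-pecking needling until the eyes become wet or developed tears", DU16 is manipulated to obtain deqi, and at Ex-HN-21 the acupuncturist "removed the needle if the sensation obtained (an electric sensation from the arm to the finger"). For sham: "The number of needles and duration of treatment in the sham acupuncture group will identical in the acupuncture group, except for any manipulations". Section 2.6 sets 12 sessions over 2 weeks.

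On sites, Table 1 (2.6.1) places DU26 "At the junction of the upper 1/3 and middle 1/3 of the philtrum", and 2.6.2 states "The sham DU26 point was 1 cun (≈20 mm) lateral to DU26". The last paragraph of 2.6.2 says instead that sham participants will probably have the same acupoints as the acupuncture group.

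The primary outcome is the NIHSS (2.7.1), whose items include "consciousness, best gaze, motor arm, facia palsy, motor leg, limb ataxia, sensation ability, dysphagia, and neglect". Section 2.7.3 has the outcome assessors document acupuncture-associated adverse events, naming bleeding, subcutaneous hemorrhage, serious pain and fainting.

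**The concern.** The sample size rests on acupuncture versus sham (2.4), so the sham blind carries the trial's main claim. The NIHSS is scored by an examiner, and several of its items depend on what the patient does when asked. If patients or assessors can often tell real from sham, the estimated difference mixes expectation with effect, and a report of a participant- and assessor-blinded result would claim more than the design delivers.

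The problem lies in what the article states, not in what it leaves out: the described technique gives one of the two blinded arms cues that the other is not meant to have, and the described adverse-event duty directs blinded assessors to the effects of needling.

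**Working it through.** **1. The stated blind set beside the stated procedures**

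| Source of information | Acupuncture | Sham | Control | Who could learn from it |
|---|---|---|---|---|
| DU26 endpoint (2.6.2) | wet eyes or tears sought | no manipulation | no needle | patient |
| DU16 endpoint (2.6.2) | deqi sought | no manipulation | no needle | patient |
| Ex-HN-21 endpoint (2.6.2) | electric sensation, arm to finger, sought | no manipulation | no needle | patient |
| Facial needle site (Table 1, 2.6.2) | midline, on the philtrum | about 20 mm lateral, or the same point under the conflicting sentence | none | assessor, if a mark is visible |
| Patient's own knowledge (2.3) | said to be blinded | said to be blinded | knows | assessor, if the patient speaks of it |
| Needle-related adverse events (2.7.3) | recorded by outcome assessors | recorded by outcome assessors | none from needling | assessor |

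The first three rows concern acupuncture versus sham and do not depend on any visible mark. They recur over up to 12 sessions. The fourth row bears on that comparison only if the sham points are lateral and a mark can be seen. The last two rows mainly separate needled patients from controls.

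**2. The plan's own sample size**

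Inputs from 2.4: post-treatment NIHSS 6.2 (SD 2.1) and 4.9 (SD 1.8); one-sided α = 0.025; β = 0.20.

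- Difference = 6.2 − 4.9 = 1.3.
- Pooled SD = √((2.1² + 1.8²)/2) = 1.956.
- n per group = 2 × 1.956² × (1.960 + 0.842)² / 1.3² = 35.5, rounded up to 36.

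This matches the stated 36. The figure does not bear on blinding; it supplies the SD for the next step.

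**3. Illustration of what a biased score would do**

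Assume no true effect and a shift of b NIHSS points in the acupuncture–sham difference from expectation or unblinded rating. The values of b are assumptions; the documents give none.

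- SE = 1.956 × √(2/n), which is 0.417 at n = 44 and 0.461 at n = 36.
- Two-sided rejection rate = 1 − Φ(1.96 − b/SE) + Φ(−1.96 − b/SE).

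| Assumed b | b as share of 1.3 | n = 44 per arm | n = 36 per arm |
|---|---|---|---|
| 0 | 0% | 5% | 5% |
| 0.2 | 15% | 0.069 + 0.007 = 7.7% | 0.063 + 0.008 = 7.2% |
| 0.3 | 23% | 0.107 + 0.004 = 11.1% | 0.095 + 0.005 = 10.0% |
| 0.5 | 38% | 0.223 + 0.001 = 22.4% | 0.191 + 0.001 = 19.2% |

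Totals come from unrounded terms. The 36 column is the number that the plan expects to be evaluable if the full 20% loss occurs.

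**The case against.** **Marks on the face.** A reader might infer that the philtrum, the lateral point and an untouched lip identify all three arms to the assessor. The documents do not support that. The needle is 0.25 mm in diameter, nothing says that it leaves a mark visible at assessment, and the article does not time the NIHSS relative to the last session. Bleeding and subcutaneous hemorrhage are listed as events to record, not as expected findings at DU26. A needled patient without a mark looks like a control. If sham uses the same acupoints, as 2.6.2 also says, the site would not separate real from sham at all. This objection stands: the facial site is a possible cue, no more.

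**Sensation is not identification.** Patients are treated at the bedside, nothing says that they are told which sensations belong to real treatment, and the electric sensation is worded conditionally. An exclusion criterion, unclear in wording, appears to deal with acupuncture in the previous 3 months. Omitting manipulation is also what makes this sham a comparator for manipulated needling. So it cannot be said that patients will know their arm. It remains true that the procedure deliberately seeks strong sensations in one arm only, so the claim of blinding needs to be tested.

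**Some protection exists, and an article condenses.** Needle number and duration are matched, and three independent research assistants evaluate outcomes. A full protocol may well hold a blinding questionnaire or assessment rules, so their absence here is not the finding. The finding is that the stated delivery and the stated recording duty work against the stated blind.

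**The error rates are assumed.** Any assumed bias inflates the false-positive rate. The figures show sensitivity to a bias; they are not evidence that one exists.

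**Conclusion.** The blinding stated in 2.3 is put at risk by the delivery in 2.6.2 and the recording duty in 2.7.3. The firmest part concerns participants: tears, deqi and an electric sensation are sought in the real arm only. For assessors, the routes are what patients may tell them, the needle-related events they must document and, possibly, the facial site. The two statements about sham points contradict each other and must be reconciled; the documents do not settle which applies.

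The size of any bias is unknown. If it reached 0.2 to 0.5 NIHSS points, the 5% two-sided error would become about 8% to 22% at 44 per arm (about 7% to 19% at 36), assuming the plan's SDs, a normal approximation and no true effect. A conclusion that the blind fails, or that marks reveal the arm, would go beyond the text. The point is a worthwhile improvement that bears on bias and on what the trial may claim. It does not invalidate the design.

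**What to change.** 1. Do the 2-week NIHSS before any session that day, with the acupuncturist absent and patients in all three arms asked not to mention needling.
2. Have existing staff other than the NIHSS assessor record needle-related adverse events, or have the assessor record them only after the NIHSS is scored and locked. Amend 2.7.3 accordingly.
3. Right after the 2-week NIHSS, record an allocation guess from the assessor and from each needled patient. Report the guesses by arm with a prespecified blinding index, and describe the acupuncture-versus-sham result as blinded only in light of it.
4. Reconcile the sentences in 2.6.2 on lateral sham points and on sham participants having the same acupoints, so that the sham that was delivered can be stated.

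The cost is two form fields, minor scheduling around the assessment visit, and a small reassignment or re-ordering of adverse-event recording. The guess measures the risk and does not remove it. Taken after 2 weeks of treatment, it may partly reflect perceived improvement, so it should be read with that caveat. None of these steps changes needling technique or treatment.

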### Outcomes and assessment procedures

2.7

Three independent research assistants will take charge of their data from baseline to 2 weeks and 3 months of follow-up and for evaluating their outcomes.

#### Primary outcomes

2.7.1

The primary outcome we chose in this study is the NIHSS score that will be measured before and after treatment to evaluate the neurological deficit. There are 15 items in the scale including consciousness, best gaze, motor arm, facia palsy, motor leg, limb ataxia, sensation ability, dysphagia, and neglect. The score of each item scores range from 0 to 4, and the total scores range from 0 to 42. A higher score indicate a more severe neurological deficit.

#### Secondary outcomes

2.7.2

Secondary outcomes included the FMA scale scores and BI. The FMA scale comprises assessments of the upper extremity (UE, 66 points) and lower extremity (LE, 34 points). The BI scale includes 10 items: continence of the bowels and bladder, dressing, entering and leaving a toilet, bathing, ascending and descending stairs, etc. We select the FMA scale to evaluate the motor function and BI to evaluate the self-care and mobility before and after treatment. In addition, the modified Rankin Scale (mRS), a scale used to evaluate the state of neurological function recovery in ACI patients, will also be assessed when the follow-up period ended (at 3 months).

#### Safety assessment

2.7.3

Acupuncture-associated adverse events will be documented by outcome assessors throughout the trial, including bleeding, subcutaneous hemorrhage, serious pain, and fainting. All adverse events will be followed up until the adverse events will be resolved.

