**Methods:**

A total of 132 patients involving four hospitals will be randomized at a 1:1:1 ratio in the acupuncture group, control group, and sham acupuncture group. All the patients will receive basic treatment, and the patients in the acupuncture and sham acupuncture groups will also receive either acupuncture or sham acupuncture treatment, respectively, at six sessions each week for a 2 weeks period, followed by 3 months of follow-up. The primary outcome will be the change in the National Institute of Health Stroke Scale (NIHSS) scores after treatment. The secondary outcomes will include the Fugl-Meyer Assessment (FMA) scale scores and the Barthel Index (BI). Adverse events that occur during the trial will be documented. To discover differentially expressed proteins (DEPs) and their roles between the ACI subjects and healthy controls, we will also perform 4D-DIA quantitative proteomics analysis, and the DEPs will be confirmed by enzyme-linked immunosorbent assay (ELISA). This study was approved by the institutional review board of the First Teaching Hospital of Tianjin University of Traditional Chinese Medicine (TYLL2023043). Written informed consent from patients is required. This trial is registered in the Chinese Clinical Trial Registry (ChiCTR2300079204). Trial results will be published in a peer-reviewed academic journal.

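### Outcome assessors who must stay blinded are assigned to record needle-related adverse events, and the article is inconsistent about which adverse events are recorded

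*Protocol article*

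**What the plan says.** On blinding, section 2.3 of the protocol article says: "All study personnel including the outcome assessors and data analysts will be blinded to the treatment allocation". For patients it says: "The participants in the acupuncture group and sham acupuncture group will be blinded, while those in the control group will not be".

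On who evaluates outcomes, section 2.7 says: "Three independent research assistants will take charge of their data from baseline to 2 weeks and 3 months of follow-up and for evaluating their outcomes".

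On safety, section 2.7.3 says: "Acupuncture-associated adverse events will be documented by outcome assessors throughout the trial, including bleeding, subcutaneous hemorrhage, serious pain, and fainting". Its next sentence is: "All adverse events will be followed up until the adverse events will be resolved". The Abstract (Methods) says: "Adverse events that occur during the trial will be documented".

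On needling, control patients receive none (section 2.3). The sham arm is needled about 20 mm lateral to each true point (section 2.6.2): "The number of needles and duration of treatment in the sham acupuncture group will identical in the acupuncture group, except for any manipulations".

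Safety is a stated aim alongside efficacy (Introduction and Discussion).

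**The concern.** Two rules conflict. One group of people is to remain unaware of allocation, and the same group is to document events defined by their link to needling, in a trial where one arm of three is not needled. The primary outcome, NIHSS, is scored by an examiner, and acupuncturists and control patients are already unblinded. Assessor blinding is therefore a main safeguard against rating bias, and once lost it cannot be restored at analysis.

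The second problem concerns the safety aim. If only events attributed to acupuncture are recorded, the control arm has none by definition, and needled-versus-control safety cannot be compared. If all events are recorded, as the Abstract suggests, it can be. A site following section 2.7.3 and a site following the Abstract would collect different data.

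**Working it through.** **Who records.** Set sections 2.3 and 2.7.3 side by side. The assessor is to be blinded. The assessor also documents acupuncture-associated events throughout the trial. To call an event acupuncture-associated, the recorder must know or ask whether the patient was needled. The answer separates the acupuncture and sham arms from control. Section 2.7 puts three research assistants in charge of outcome evaluation from baseline to 3 months, and the article names no other safety recorder.

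**What an event reveals, by comparison.**

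| Comparison | Needled? | What a recorded needle event shows |
|---|---|---|
| Acupuncture or sham vs control | yes vs no | The patient is not in the control arm |
| Acupuncture vs sham | yes vs yes | Nothing by itself; the site of a bleed or bruise, or pain from manipulation, may be a clue |

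The clues in the second row come from section 2.6.2: different needle sites, and manipulation only in the true arm. One true point (DU26) is on the philtrum, and NIHSS includes a facial palsy item, so the rater examines that area.

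**Which events.** Section 2.7.3, first sentence: acupuncture-associated events. Section 2.7.3, second sentence: follow-up of all adverse events. Abstract: adverse events during the trial, with no restriction. Under the first rule, the 44 control patients can contribute 0 events by definition. Under the other two they can contribute events.

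**Size.** The point rests on no figure in the plan, but the plan's inputs give a scale. Section 2.4 states 6.2 (SD 2.1) and 4.9 (SD 1.8), one-sided alpha 0.025 and power 80%.

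- Difference: 6.2 − 4.9 = 1.3 points.
- n per group = (1.960 + 0.842)² × (2.1² + 1.8²) / 1.3² = 7.85 × 7.65 / 1.69 = 35.5, so 36. The plan's 36 is reproduced, and 36 × 1.20 = 43.2 gives its 44.
- Standard error of a difference with 36 per arm: √((2.1² + 1.8²)/36) = √0.2125 = 0.461.

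The article gives no adverse event rate, no unblinding rate and no rating bias, so the following inputs are assumptions. Let f be the share of needled patients with a recorded needle event, and b the shift in NIHSS that a rater applies to them. The arm mean moves by f × b.

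| f | b (points) | f × b | Share of 1.3 |
|---|---|---|---|
| 5% | 0.5 | 0.025 | 2% |
| 10% | 1.0 | 0.10 | 8% |
| 20% | 1.0 | 0.20 | 15% |
| 30% | 1.0 | 0.30 | 23% |

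Two-sided type I error at nominal 5%, with bias expressed in standard errors:

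- Upper end: 0.30/0.461 = 0.65, and Φ(−1.96 + 0.65) + Φ(−1.96 − 0.65) = 0.095 + 0.005 = 0.10.
- Lower end: 0.025/0.461 = 0.05, and Φ(−1.91) + Φ(−2.01) = 0.028 + 0.022 = 0.05, in effect unchanged.

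Applied to acupuncture versus control, this also assumes that the SDs in section 2.4 carry over to that pair. Applied to acupuncture versus sham, it needs the rater to tell the two arms apart. If needled patients in both arms are shifted alike, the shift cancels.

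**The case against.** The strongest reply is that the comparison used for the sample size is acupuncture versus sham. Both arms get the same number of needles for the same time, so bleeding, bruising, pain or fainting can occur in either. Nothing says that assessors attend treatment sessions. A reader might infer that the rule breaks the NIHSS blind for the powered comparison. The documents do not support that: they show clues, not disclosure. This part of the reply stands, but it leaves the exposure of needled versus control untouched.

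The second reply is that the article does not say that only attributed events are kept. This also stands: the Abstract and the second sentence of section 2.7.3 are wider. It makes the defect an inconsistency of scope, not a decision to omit events. Nor are all safety comparisons lost. Acupuncture versus sham stays broadly comparable even under the narrow rule, and the zero concerns the control arm only.

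A reader might also infer that sham patients are unblinded by "The patients will be informed whether they will receive acupuncture treatment or not". That reading is not needed. Section 2.6 describes both needled arms as receiving acupuncture therapy, and section 2.3 describes control as receiving none. The very next sentence blinds the two needled arms but not control. The sentence can simply mean needled or not needled.

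Finally, it may be said that a journal article condenses a fuller protocol. That would excuse silence about a safety recorder. It does not excuse assigning the task to the blinded assessors.

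**Conclusion.** The point holds in limited form. Sections 2.3 and 2.7.3 cannot both be followed as written without exposing needled-versus-control allocation to the raters of NIHSS, FMA, BI and mRS. For acupuncture versus sham there is a foreseeable risk from needle site and pain from manipulation, and no demonstrated break. The scope of adverse event recording is inconsistent between the Abstract and section 2.7.3, and under the narrow rule safety cannot be compared between the needled arms and control.

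The size of any bias is unknown. The range of 0.025 to 0.30 points rests wholly on assumed event rates (5 to 30%) and rating shifts (0.5 to 1.0 point). The 10% type I error belongs to the upper corner of that range and should not be quoted as an expected value. The conclusion does not depend on it.

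**What to change.** 1. In section 2.7.3, assign adverse event recording to trial or ward staff who do not score NIHSS, FMA, BI or mRS, and keep the raters away from safety forms. The acupuncturists are a poor choice: they deliver the treatment and have no stated role in the control arm, so events could be ascertained unequally.
2. Record all adverse events regardless of cause in all three arms, with the same form, questions and schedule. Judge relatedness to needling in a separate step, and compare rates by arm.
3. Reconcile the Abstract, section 2.3 and section 2.7.3 so that they agree on who records and what is recorded.

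The cost is wording in the protocol and case report form, and more adverse event forms, mainly in the control arm. If existing staff can take the task, no new posts are needed; the article does not describe staffing, so the sponsor should confirm this. Sample size, power and alpha are unaffected.
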